Teacher characteristics that may affect program effectiveness include demographic characteristics (e.g., age, gender, ethnic identity) and other factors (e.g., years of experience). Previous meta-analytic studies examining the associations between student–teacher relationships and school adjustment showed that teachers’ gender and ethnicity moderated these associations [27, 28]. For example, female teachers might be able to better implement socioemotional programs, due to the traditional gender role of females as effective caretakers of child development [27]. In addition, experienced or older teachers might be more effective in implementing the program because they have more knowledge and have acquired greater skill. Indeed, previous research showed that teaching experience is positively related to student outcomes (e.g., achievement, motivation) [29]. School characteristics, such as years of experience with a social safety program (e.g., KiVa), school or class size, or location may moderate the effectiveness of the program. In line with this reasoning, if schools already have (much) experience with implementing social safety programs, it is likely that teachers at those schools may be more effective in implementing the current program. Furthermore, it is likely that teachers give students more individual attention in smaller classes, which might be important during classroom-based intervention programs and hence, may result in stronger effects. Program effectiveness may also differ based on location, as a previous meta-analysis examining the effectiveness of family interventions demonstrated smaller effects for urban settings compared to nonurban settings [30].

Program characteristics that may affect program effectiveness include program integrity and working elements. Program integrity, whether the intervention is implemented as originally planned, is important to report and to investigate as moderator of effectiveness, as it is necessary to draw conclusions about an intervention program. Negative or nonsignificant results might be due to incorrect program implementation, and not because of an ineffective program [31]. In addition, whether the working elements (i.e., meaningful roles, classroom meetings, and compliments) were implemented and how often may influence program effectiveness. Indeed, previous literature demonstrated that better implementation of school-based prevention programs is associated with more beneficial outcomes [15, 32].

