### Control condition

The control condition will not receive any material or training concerning Meaningful Roles during the implementation of the program in the intervention condition (treatment-as-usual, TAU). Schools in the control condition are given the option to receive the materials and training to implement the intervention at a later stage, after the data collection is finished.

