
*Civic skills* will be assessed at all three timepoints, for teachers only. Specific questions were developed for this study, based on the questionnaire measuring citizenship ([Vragenlijst Burgerschap Meten]; [50]). Four domains will be assessed by asking teachers how the children in their class: 1) act democratically (e.g. “accept decisions made by the whole class (majority decisions)”, 2) act socially responsible (e.g., “stand up for each other”), 3) dealing with conflicts (e.g., “consider the other person in a conflict when looking for a solution”, and 4) dealing with differences (e.g., “are curious about what other children are good at (qualities)”. Higher scores reflect more (positive) civic skills in the classroom.

*Teacher attitudes* will be assessed at all three timepoints, with specific questionnaires developed for this study. Teachers are asked what they find important in their job as a teacher to stimulate, for example: “that children help each other in the classroom”. Higher scores reflect a positive attitude of stimulating prosocial behavior and STD components.

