#### Moderators

*Child, teacher, and school characteristics* will be collected at baseline. Child characteristics include age, gender, romantic attraction (i.e., possibility of falling in love with a boy/girl), grade, and ethnic identity. Teacher characteristics include age, gender, years of experience (as a teacher in general, and as a teacher at the specific school) and experience with implementing social safety programs, as well as attitudes of the teachers. School characteristics include location, number of participating grades and students in the classrooms, and years of experience with a social safety program (e.g., KiVa).

*Working elements* will be assessed halfway through the program (T2) and after completion of the program (T3), with specific questions developed for this study. Children and teachers fill in questionnaires related to the three main components of the program: 1) meaningful roles (e.g., “How much did you like the role(s)”, “Which roles were the most popular?”, respectively), 2) classroom meetings (e.g., “The weekly meetings were done independently by the class”, “How often has a meeting been held?”, respectively), and 3) compliments (e.g., “I have received compliments from my classmates”, “How many times a week has attention been paid to the compliments?”, respectively). Higher scores reflect a more positive or greater adherence of the working elements.

*Program integrity* will be assessed halfway through the program and after completion of the program, with specific questions developed for this study. Teachers and school leaders fill in (open and closed) questionnaires related to the implementation of the program, divided into the domains training and material (e.g., “How often have you used the manual?”), child questionnaires (e.g., “Where there any questions that the children struggled with?”), time investment (e.g., “How did you feel about the time you had to implement the program properly?”), and global impression (e.g., “What is your general impression of the degree of success of the implementation of the program?”). Higher scores reflect a more positive or greater adherence of the program.

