### Statistical analyses

Before the analyses, possible baseline (T1) differences in demographics and outcome variables (baseline assessment) between children in the intervention program and the control condition will be checked with ANOVA (continuous variables) and chi-square analyses (categorical variables). To investigate the effectiveness of the intervention program, regression analyses will be performed. The dependent variables are the outcome measures at intermediate (T2) or posttest (T3), condition is the predictor variable (1 = intervention, 0 = control), and baseline (T1), potential differences between the experimental and control group at T1, or intermediate measures (when dependent variables are the outcome measures at T2) are the covariates. The effect of potential moderators (categorial or continuous) on the outcomes will be examined by adding interaction effects to the models.

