## Discussion

This study protocol presents the design of a cluster RCT to investigate the effectiveness of a classroom-based program, Meaningful Roles, to promote a more prosocial classroom climate in primary schools, through improving intrinsic motivation to behave prosocial, by enhancing SDT components (i.e., social autonomy, social competence, and social relatedness). This is important, because a positive, prosocial classroom climate is associated with an optimal learning environment, as well as positive school quality and wellbeing in children [1, 2]. Previous research showed improved prosocial classroom climate (e.g., increased prosocial behavior) in youth after receiving school- or classroom-based social-emotional focused programs (e.g., [11, 15]), as well as improved psychological health after receiving programs focused on STD components [22]. To overcome limitations of previous research, including suboptimal study design (e.g., non-randomization) and target group (e.g., US samples), we will examine a classroom-based approach for upper primary school students and use a cluster RCT to exclude confounding (e.g., allocation and selection bias) as much as possible. We will use a multi-informant (i.e., child, teacher, school leader) and multi-method (i.e., questionnaires and focus groups) approach. Moreover, we strive to use a large, diverse sample, that could allow us to examine potential moderators of program effectiveness (i.e., child, teacher, school, and program characteristics, i.e., working elements and program integrity).

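### Program integrity and the working elements are planned as moderators through interaction terms, but they are measured only after randomisation and concern a program control schools do not receive, so those interactions are either not identifiable or do not show effect moderation

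*Protocol article*

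**What the plan says.** **Method.** The Statistical analyses section regresses each outcome at T2 or T3 on trial arm: "condition is the predictor variable (1 = intervention, 0 = control"). Its covariates are baseline values, T1 differences between the arms, and intermediate measures. Moderators get a single sentence: "The effect of potential moderators (categorial or continuous) on the outcomes will be examined by adding interaction effects to the models". No other quantitative method is given for any moderator.

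**Which variables are moderators.** The Background says program integrity "is important to report and to investigate as moderator of effectiveness". The Discussion says the sample could allow the study to "examine potential moderators of program effectiveness (i.e., child, teacher, school, and program characteristics, i.e., working elements and program integrity"). Table 1 labels the three working elements as outcome and moderator, and integrity as moderator and covariate.

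**When they are measured.** Under Moderators, the working elements "will be assessed halfway through the program (T2) and after completion of the program (T3), with specific questions developed for this study", and program integrity "will be assessed halfway through the program and after completion of the program, with specific questions developed for this study". Table 1 agrees: T2 and T3, no T1. Child, teacher and school characteristics are collected at baseline.

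**Who has the program.** The Control condition section states: "The control condition will not receive any material or training concerning Meaningful Roles during the implementation of the program" in the intervention arm.

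**The concern.** A moderator of effectiveness describes for whom, or under what conditions, the difference between arms is larger or smaller. To estimate that, the moderator needs a value in both arms that does not depend on the arm. Integrity and the working elements do not meet this requirement. The integrity items ask about use of the program manual, time available to deliver the program, and how well delivery succeeded. The role items ask how much children liked their roles. A treatment-as-usual school has no answer to either.

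At stake is part of the second aim in the Current study section, which names program integrity as a moderator. The only estimable quantity is a slope among intervention schools. Well-functioning classes may both deliver the program better and score better on the outcomes, so that slope is open to confounding. The Background also suggests that a null result might reflect poor implementation rather than an ineffective program. A confounded integrity slope reported as moderation could then be used to explain away a null randomised comparison.

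**Working it through.** **1. The plan's own figure.** The Study sample section gives 42 schools (21 per arm) for power 0.80, alpha 0.05 and effect size 0.21, and says this also suffices for moderators. With individual randomisation, two-sided:

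n per arm = 2(1.960 + 0.842)² / 0.21² ≈ 356.

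With m children per school, 21 schools per arm reach power 0.80 if ICC ≤ (21m/356 − 1)/(m − 1). This is about 0.010 for m = 20, 0.035 for m = 40, 0.047 for m = 80 and 0.050 for m = 100. The article gives neither m nor the ICC, so 42 can be neither confirmed nor refuted. The point below does not depend on it.

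**2. The model implied.** Let Z be condition (1/0) and M the integrity or working-element score. Leaving out the T1 covariates:

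E[Y] = b0 + b1·Z + b2·M + b3·Z·M

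Moderation of the program effect is b3. The article does not write out Z·M. But Z is the only predictor named and the moderators are of program effectiveness, so no other reading fits.

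**3. M missing in control schools.** Complete-case fitting drops all 21 control schools. Z then equals 1 in every remaining row, so Z repeats the intercept and Z·M repeats M. The columns [1, Z, M, Z·M] have rank 2 of 4. Neither b1 nor b3 can be estimated.

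**4. M coded 0 in control schools.** In intervention rows Z·M = M. In control rows Z·M = 0 = M. The two columns are identical. A numerical check with 42 schools (21 per arm) gave rank 3 of 4. Only the sum b2 + b3 is estimable, and that is the slope of M among intervention schools. Any other constant c fares no better, because Z·M = M − c + c·Z in every row, and the rank is still 3.

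**5. M asked in both arms.** Some items, such as how often a class meeting was held or whether compliments were received, make sense in a control class. The Data collection section does not say whether control classes get them. If they do, b3 can be computed. But a given score is reached with the program in one arm and without it in the other, so classes with equal M are not comparable across arms. Table 1 itself also labels the working elements as outcomes. A difference in slopes on a variable that assignment changes does not validly show effect moderation.

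**6. What the within-arm slope can look like.** This is an illustration with assumed inputs: 42 schools, 2,000 runs, true moderation 0, condition effect 0.21. A latent school quality correlates 0.5 with fidelity and adds 0.15 per SD to the outcome; school-level residual SD is 0.25.

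| Analysis | Mean estimate | Share with p < 0.05 |
|---|---|---|
| Fidelity slope, intervention schools only | 0.075 | 21% |
| Condition × would-be fidelity, if known in both arms | 0.000 | 5.5% |

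The first row agrees with the algebra: 0.15 × 0.5 = 0.075. The second row shows that the false signal comes from having no control-arm counterpart, not from the interaction method as such. The second analysis is not available in this trial. No T1 adjustment was simulated; it would lower the 21% to the extent that baseline values capture school quality.

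**The case against.** The strongest defence is that the article never says how control schools are scored. With 0 in control, software drops the redundant column and what remains is the within-intervention slope, essentially the dose-response analysis recommended here. On that view the fault is one of labelling, and an article may leave coding to the analysis plan. Part of this stands: the remedy is wording, and no new data are needed. But the article does more than stay silent. It assigns these post-randomisation variables the role of moderator and gives one rule for all moderators. An analysis plan that follows the rule inherits the fault; one that corrects it departs from the article.

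Four stronger readings are tempting, and the documents do not support them.

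- **Teacher attitudes are a post-treatment moderator.** A reader might infer this because attitudes "will be assessed at all three timepoints, with specific questionnaires developed for this study". That sentence stands under Secondary outcomes. The Moderators section lists attitudes among the characteristics collected at baseline, so the T2 and T3 values fit their second role as an outcome.
- **Civic skills are a post-treatment moderator.** The only basis is a Table 1 label. A T1 value exists, and nothing says later values will be used as the moderator.
- **Integrity will be a covariate in the effect model.** Table 1 gives it that label, but the covariates listed under Statistical analyses do not include it. This is a mismatch to reconcile, not a planned adjustment.
- **None of the four interactions can be estimated.** That is strict for integrity and meaningful roles. For meeting and compliment items it depends on whether control classes are asked, and if they are, the problem is post-treatment bias.

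**Conclusion.** The point holds for program integrity and the three working elements. For integrity and meaningful roles, the condition-by-moderator term is not identifiable under the stated rule: the control arm is lost, or the design matrix has rank 3 of 4. This follows from the columns alone and needs no assumption beyond control schools having no program to score. For meeting and compliment items also put to control classes, the term is estimable but is not valid evidence of moderation.

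The randomised condition effect is untouched as long as integrity stays out of that model, and the baseline child, teacher and school moderators are unaffected. The 21% figure rests on assumed inputs and shows only the direction in which a within-arm slope can mislead; it is not an estimate for this trial.

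**What to change.** Before analysis:

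1. Limit condition-by-moderator models to variables measured at T1: child, teacher and school characteristics, teacher attitudes at T1 (as the Moderators section already implies) and civic skills at T1.
2. Analyse integrity and the working elements within the intervention arm as a dose-response, adjusted for T1 outcome values and allowing for clustering by class and school, and label it associational. It draws on 21 schools.
3. If a causal statement about implementation is wanted, prespecify a complier-type instrumental-variable analysis with randomisation as instrument and adherence 0 in control. State its assumptions, above all that assignment affects outcomes only through the implementation measured. It answers a different question from moderation.
4. State whether control classes receive the meeting and compliment items. If so, report them by arm as outcomes, not as moderators.
5. Reconcile the covariate label for integrity in Table 1 with the Statistical analyses section, so that integrity stays out of the condition-effect model.

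The cost is wording only, with no change to recruitment or data collection. The price is that findings on integrity and working elements become non-randomised evidence and must be reported as such.

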## Discussion

This study protocol presents the design of a cluster RCT to investigate the effectiveness of a classroom-based program, Meaningful Roles, to promote a more prosocial classroom climate in primary schools, through improving intrinsic motivation to behave prosocial, by enhancing SDT components (i.e., social autonomy, social competence, and social relatedness). This is important, because a positive, prosocial classroom climate is associated with an optimal learning environment, as well as positive school quality and wellbeing in children [1, 2]. Previous research showed improved prosocial classroom climate (e.g., increased prosocial behavior) in youth after receiving school- or classroom-based social-emotional focused programs (e.g., [11, 15]), as well as improved psychological health after receiving programs focused on STD components [22]. To overcome limitations of previous research, including suboptimal study design (e.g., non-randomization) and target group (e.g., US samples), we will examine a classroom-based approach for upper primary school students and use a cluster RCT to exclude confounding (e.g., allocation and selection bias) as much as possible. We will use a multi-informant (i.e., child, teacher, school leader) and multi-method (i.e., questionnaires and focus groups) approach. Moreover, we strive to use a large, diverse sample, that could allow us to examine potential moderators of program effectiveness (i.e., child, teacher, school, and program characteristics, i.e., working elements and program integrity).

There are several challenges in this study, such as the recruitment of a sufficient number of schools (and students) and the collaboration with multiple parties. First, it may be difficult to recruit sufficient schools with a diverse and representative sample of students and maintain the involvement of schools, teachers, students, and parents over the course of the study. Recruitment of schools may be difficult because we would preferably like schools to participate with all their upper classes (groups 5–8), which requires involvement and participation of multiple teachers (who all need to stand behind the program and research). To recruit schools, we will mainly try to contact schools who already have connections or collaborations with the research or implementation team (i.e., KiVa schools), making the first contact easier. These schools are located all throughout the Netherlands. As such, it is likely that diverse schools, with a diverse sample of students, will be represented in our study. Additionally, flyers will be distributed via mail and newsletters, and information meetings will be organized to give more information about the program and study participation.

Second, since participation of students requires active informed consent from their parents, it is crucial that all parents of participating classes are reached and are provided with clear information about study participation. Participating schools make sure that parents receive information about the project, and teachers will be responsible for contacting parents (e.g., face-to-face, mail, telephone). In order to make giving permission as easy as possible, parents can also give digital consent. Researchers and the contact person of the schools will be in constant contact to increase response rates. These precautions are expected to increase the likelihood of participation of students.

Third, another challenge in this study is the participation and involvement of multiple parties, including the researchers, the implementation team, trainers, schools, teachers, parents, and students. To strengthen the collaboration between parties, we will sign multiple agreement forms (e.g., data processing agreement, collaboration agreement). Moreover, we will organize regular meetings (between the research and implementation team) and give weekly updates about recruitment rates (to schools and teachers). Moreover, we will be available for schools for consultation at any time during the recruitment phase and implementation process. It is of crucial importance that we invest time in clear and timely communication with all parties in order to collaborate as effectively as possible. Furthermore, we try to work according to a standardized research protocol as much as possible, but will tailor it to the needs of the specific schools (e.g., regarding recruitment strategy, for instance using paper or digital informed consent forms). This way, we aim to avoid miscommunications and will ensure a positive and fruitful collaboration.

In sum, the current protocol describes a study that will examine the effectiveness of a classroom-based program, Meaningful Roles, in promoting a prosocial classroom climate in primary schools. It is of crucial importance that classrooms are a safe and positive environment for children to be in, to improve social competence and achievement, and prevent the development of mental health problems and dysfunction later in life.

## Data Availability

The data obtained in the current study will become publicly available after publication of the results on the main research questions. The data will be archived on the DANS Easy environment from the KNVB as agreed upon with NWO (open access policy). The corresponding author can be contacted for more information.
